# Study Procedures

## 4.1 Study Design

This is a clinical trial with a participant-blinded, cross-over study design with repeated-measures assessments will take place at each site. Short-term, in-lab sessions will be used to address Aim 1 (i.e., comparing in-lab *emulator* trials to in-lab corresponding *actual* AFO trials) and the Exploratory Aim (comparing in-lab patient-optimized emulator trials to in-lab prescribed *actual* AFO trials). Aim 2 will compare short-term in-lab trials with longer-term follow-up using corresponding *actual* AFOs. We will assess user preference, satisfaction, perceived mobility and performance in *emulated* and *actual* AFOs to determine whether the emulator and/or a brief trial of *actual* AFOs can predict user mobility and AFO preference following longer term use in the community environment.

See section 5.5 below for data collection procedures.

## 4.2 Recruitment Methods

The study will recruit up to 56 participants with lower limb musculoskeletal trauma who are currently using an AFO. Men and women will both be recruited to the extent they are represented in the patient population. No exclusions will be made on the basis of race, ethnicity, sex, or gender.

Human subjects will be recruited from a convenience sample of eligible participants at the sites. The sites were specifically selected based on their potential for high enrollment and because they prescribe a wide range of AFO devices to patients of various mobility/activity levels and injury etiologies.

The following methods and resources may be used to recruit subjects:

1. Recruitment using medical record data is often believed to be the most effective means of achieving enrollment goals [21]. Designated research staff at the sites will screen relevant clinic lists in computerized patient record systems to identify potential participants. After review of relevant clinic lists, designated staff will go to the clinic or contact providers to ask if a patient might be a good fit for the study. If the clinician agrees that a patient may be an appropriate study participant, during an appointment the clinician will ask the patient if she/he is interested in speaking with designated study staff; patients will be given a chance to opt out. For patients who are interested, designated study staff will speak to potential participants.

2. **Clinician Referral:** The study teams at each site have built relationships with local clinic staff and have established effective clinical referral systems. Research staff will inform providers working in relevant clinics about the study and inclusion/exclusion criteria so they can refer potential participants to contact the study team. Flyers and business cards may be provided to clinicians to give to patients that are interested in the study. If a clinician informs patients about the study and the patient agrees to be contacted about it, the clinician may provide the research team with the patient’s name and they may also provide contact information. Clinicians may also provide (via in-person/on the phone) the names of patients that they are aware of who may be a good fit for the study and a study staff member will send an approach letter, make direct contact during a clinic visit, or the clinician provider may inform potential participants.

3. **Flyers:** Approved flyers may be posted in designated areas at the sites. Flyers will also be posted and distributed to potential subjects at various locations. Permission will be obtained prior to posting flyers in these clinics. Clinicians and support staff will direct interested individuals to contact the study staff to learn more about the study. The flyers may also be re-sized to be used in print publications or as a complete image in online ads. QR codes may be used on flyers so participants can take a picture and then a pre- populated email can be sent to the research team to identify an individual’s interest in a particular study. Recruitment advertisements may also be in print and online publications, as permitted by the IRB.

4. **Participant Registries:** Applicable patient registries maybe also be used for recruitment. The registries would also include participants that were screened and/or participated in previous studies and includes lower limb prosthetics and orthotics users. Designated study staff may also speak with these potential participants in-person if they have an upcoming clinic visit.

Payment of Participants

Each participating site may advertise via different recruitment efforts. Participants may be paid up to $500 total for study participation by HJF. Payment will be dispensed after completing each research milestone. There is no cost to patients for the research tests, procedures/evaluations, and study product while taking part in this trial. Procedures and treatment for routine clinical care not directly associated with the study including costs associated with hospital stay may be billed to the patient, patient’s insurance, or third party.

| Payment Schedule | | |
| --- | --- | --- |
| Study Visit 1 | Study introduction, screening, consent, casting | $50 |
| Fittings | AFO fittings (if required, 1-2 sessions) | $30 each |
| Study Visits 2-3 | In-lab testing sessions | $80 each |
| Study Visits 4-6 | In-Lab testing sessions following 2-week trials | $50 each |
| Study Visits 7 | In-lab exploratory testing session (optional) | $80 |
| Total |  | $360-500 |

## 4.3 Informed Consent Procedures

A waiver of informed consent and HIPAA authorization will be used for initial recruitment and screening purposes. A waiver of documentation of consent and HIPAA authorization will be used to retain the preliminary eligibility screening responses. Informed consent will be obtained prior to enrollment in the study. A member of the research team will conduct the informed consent process and screening based on the inclusion and exclusion criteria above.

## 4.4 Inclusion/Exclusion Criteria

**Inclusion Criteria**

- lower extremity injury requiring current use of an AFO
- unlimited community ambulators [22]
- age 18-65 years
- 100-250 lbs
- at least 2 weeks’ experience using an AFO
- ankle/foot pain over the last week on the foot which you wear an AFO, asked at screening: average resting pain <1/5; average pain with activity <2/5
- U.S. Men’s foot size 7-13
- >10 degrees sagittal plane ankle range of motion
- English speaking
- able to comply with study procedures

**Exclusion Criteria**

- known cognitive impairment (e.g. diagnoses such as moderate/severe traumatic brain injury, dementia)
- inability to comply with instructions
- medical conditions that would preclude safe involvement
- unable to provide written informed consent
- pregnant (as per self-report)
- prior history of stroke
- use of an assistive device such as a walker or cane

## 4.5 Study Evaluations

Prior to enrolling and consenting, participants must meet the inclusion criteria described above. Once consented, AFOs will be fit to each subject at an initial visit, based on manufacturer recommendations for foot size and body weight. Additional fitting sessions may be utilized to ensure a good fit to the individual for all three actual AFOs to be evaluated.

Participants will undergo up to three in-lab sessions: testing the emulated AFOs, testing the actual AFOs, and an optional exploratory aim session of user-selected AFO properties. Participants will undergo three 2-week periods where participants will be instructed to wear the study AFO instead of their clinically-prescribed AFO for all usual activities of daily living. After two weeks of wearing each AFO, participants will return to the laboratory for follow-up evaluation (Figure 1). Injury history and participant demographics will be collected at the initial intake session.

Participants will be block randomized to ensure similar numbers of participants are assigned to each of three AFO testing sequences and similar numbers of participants undergo either the emulated in-lab session or actual AFO in-lab session first.

**Emulated AFO testing session**. Participants will begin by walking on a treadmill in the emulator to become accustomed to its use. Participants will wear the emulator’s end effector the way they would their clinically prescribed AFO and the study orthotist will be present to make any necessary adjustments. The emulator parameters will be adjusted by the research staff member in real-time as the subject walks so they experience the range of emulated AFO conditions to be tested. After the emulator accommodation period, participants will trial three emulated AFOs in a randomized order. Participants will complete an Activities Trial and patient reported outcomes (described below).

**Actual AFO testing session.** Prior to the start of the testing session, participants will be fit with the three actual AFOs to be worn during the data collection. Fitting will be done according to the routine standard of clinical care (e.g. test device for the custom AFOs). On the day participants complete the actual AFO testing, they will walk on the treadmill in each AFO condition to acclimate prior to testing. Then, participants will undergo the same Activities Trial as in the emulated AFO testing session (described below). The same questionnaires will be completed to identify patient-reported outcomes. In the actual AFO testing session, participants will additionally complete a series of performance tests described below.

**Two-week follow up sessions**. Participants will complete two-week long community trials in each of the three actual AFO conditions in a randomized. AFOs will have already been fit to each subject as described above. Participants will be instructed to wear the study AFO instead of their clinically-prescribed AFO for all usual activities of daily living. After two weeks of wearing each AFO, participants will return to the laboratory for follow-up evaluation; Patient-Reported Outcomes and Performance Tests will be assessed. A subset of participants may also have the activities trial collected and/or gait biomechanics collected at the two-week follow up sessions.

**The Exploratory Session** will compare a participant’s clinically prescribed AFO (clinician optimized) to a participant-optimized setting on the emulator. Stiffness will be the optimized parameter. In this exploration, participants will be allowed to dial in and change the stiffness parameters on the emulator so that they self-identify an optimal value (patient-optimized).

**Figure 1.** Study Overview

**
[figure not shown]
**

**Activities Trial**. The activities selected are intended to represent a range of activities commonly encountered in the community environment (Table 1). As detailed below, activities will be assigned in a manner specific and appropriate to the individual patient (e.g., participants of a lower mobility or with contraindications will not be asked to run). Each speed and activity condition will take place for at least 30-seconds and rest will be provided between activities as needed. After each AFO condition is complete, participants will rest for at least 10 minutes before engaging in the next AFO condition.

| **Activities Trial** |
| --- |
| Walking on a level treadmill at 3 standardized speeds based on leg length [23] |
| Walking uphill on a treadmill at a comfortable speed |
| Walking downhill on a treadmill at a comfortable speed |
| Walking up a stairmill at a comfortable pace (optional) |
| Running on a treadmill at a comfortable speed (optional) |

**Table 1.** Activities trial conditions

During the activities trials we will collect gait biomechanics. Participants will be asked to change into a tight-fitting shirt and shorts that we can provide. A private area for participants to change clothes will be provided. We will record a series of standard body measurements such as height, weight, and lengths of segments. We will attach up to 70 reflective makers using double sided tape and wrap to the participant’s body segments and joints. During the tests in the lab, the cameras will record the location and movement of the markers; they do not record a picture of the body. Ground reaction force data will be collected from an instrumented treadmill during treadmill walking.

**Patient-Reported Outcomes.** Participants will complete a series of questionnaires to assess patient-reported outcomes. Some of the questions in these instruments are not sensitive to a short-term trial and may be excluded or modified (see descriptions below).

• **AFO Preference**. Preference is the primary outcome measure. Preference for a given condition will be assessed using a 10-point scale ranging from “Do not like at all” to “Like very much”. Each participant will be asked to rate his or her preference during each specific trialed activity. During in-lab testing, preference will be assessed at the conclusion of the Activities Trial. Additional information of the user’s assessment of the AFO stiffness ranging from “Far too stiff” to “Far too soft” and whether they would wear the device on a daily basis will be collected.

• **AFO Comparison**. Ranked preference and perceived AFO stiffness will be collected at the actual and emulated in-lab session between the three braces trialed and following the third community take home trial.

• **Rating of Perceived Exertion** (RPE). RPE will be recorded on a CR 10 Borg scale [24, 25]. RPE will be recorded after each activity in the Activities Trial and after the 2-Minute Walk Test (see below).

• **Pain**. Ankle/foot pain on the limb with the AFO will also be scored using on an 5-point scale (1 - no pain to 5 – very severe). Pain will be recorded after each activity in the Activities Trial and after the 2-minute-walk-test (see below). During the community trial phase, pain will be assessed at the conclusion of each two-week AFO trial period. Pain will also be assessed as a screening measure (see inclusion/exclusion criteria). using the PROMIS Pain Intensity (short form 3a) and Interference subscale (short form 6b). During the community trial phase, pain intensity and interference will reflect the past seven days. The PROMIS Pain Intensity and Pain Interference subscales are universal, rather than disease specific, have high reliability, and high construct validity with related health outcomes [26].

• **Activities-Specific Balance Confidence Scale** (ABC-5 Scale). The ABC-5 Scale is a subjective measure of confidence in balance or unsteadiness when performing a variety of movements. These movements are specific to activities of daily living. It can be used to assess fall risk among cohorts of individuals with balance limitations. For example, scores of <67% indicate a risk for falling and can accurately classify individuals who fall 84% of the time [27]. This scale has been used in a wide variety of patient populations with lower limb impairments, including individuals with lower limb trauma, such as amputation [28, 29]. The ABC will be assessed at intake to characterize the participant cohort. The questions relating to walking around the house (substitute “treadmill”), walking up stairs, and walking up and down a ramp will be used for in-lab testing and the ABC will be assessed at the conclusion of the Activities Trial in each AFO condition. During the community trial phase, the full ABC will be assessed at the conclusion of each two-week AFO trial period.

• **Quebec User Evaluation of Satisfaction with assistive Technology** (QUEST 2.0). The QUEST 2.0 evaluates a user’s satisfaction with various assistive technologies [30]. This 12-item instrument incorporates eight items to assess characteristics in terms of 1) size, 2) weight, 3) adjustments, 4) safety, 5) durability, 6) simplicity of use, 7) comfort, and 8) effectiveness. Subjects are asked to rate their satisfaction for the device on a five point scale. Four additional items related to service include 9) service delivery, 10) repairs and service of the device, 11) professionalism of service, 12) follow-up service will not be assessed as part of this study. Subjects are asked to choose the three most important items related to their assistive device. The QUEST 2.0 has been used in a variety of patient populations with lower limb injuries, including individuals with amputation [31] and in a range of orthotic applications [32]. The QUEST will be assessed at the start of the initial session to characterize the participant cohort. The QUEST will also be assessed at the conclusion of each two-week AFO trial period.

• **Orthotics and Prosthetics Users’ Survey** (OPUS). The OPUS is a self-report questionnaire consisting of five modules [33]. In the proposed work, we will be incorporating the following two modules related to the lower extremity: 1) Lower Extremity Functional Status Measure and 2) OPUS- Satisfaction with Devices and Services (questions 1-11 only). The first is based on a five-point Likert scale and nominal Yes/No scale while the second uses a six-point Likert scale. The OPUS can be used in all ages and with unilateral or bilateral prosthetic/orthotic users, congenital or acquired populations, and with all levels of orthosis and/or prosthesis use. The OPUS will be assessed at the start of the initial session to characterize the participant cohort. During the in-lab testing, the OPUS Lower Extremity Functional Status Measure questions relating to balance while standing, walking around indoors, walking up a ramp, and climbing a flight of stairs will be used. All questions will be assessed following each community trial test All questions relating to satisfaction with device (1-11) will be used after each community trial test.

• **Orthotic Patient Reported Outcomes – Mobility** (OPRO-M). The OPRO-M is a self-report 20 item questionnaire (publications in preparation) examining the ability of the participant to complete a range of challenging everyday mobility tasks with their assistive device(s). The OPRO-M is based on a five-point Likert scale. The OPRO-M will be assessed at the start of the initial session to characterize the participant cohort and following each community trial test.

• **Self-Reported Wear Time.** The participant will be asked to record approximately how many hour the study brace/AFO was worn during each day of the take home period.

• **Feedback.** The participant will be asked to provide any feedback they may have on the study, their participation in the study, or the braces used at the conclusion of their participation in the study.

**Performance Tests**. Participants will complete a series of performance tests. These measures each relate to the questionnaire-based measures described above. For example, the Narrowing Beam Walking Test objectively measures balance while the ABC subjectively infers balance from self-report.

• **Two-Minute Walk Test** (2MWT). The 2MWT assesses walking ability. Participants will be asked to walk the greatest distance they can in 2 minutes while walking a 15.2m ‘out and back’ course until asked to stop [34]. The distance walked will be recorded as will the post-test rate of perceived exertion (Borg CR 10 scale) [35]. The 2MWT has been routinely as part of prosthetics and orthotics research. The 2MWT has been found to be valid and reliable in multiple diagnostic groups including those with lower limb amputation, neurologic impairment and others [36]. Meta-analyses and reviews report improvements in walking and mobility as a result of AFO use, so it is reasonable to expect that improvements in these areas [37-39].

• **Four-Square-Step-Test** (FSST). The FSST is a test of balance and agility [40] where the patient must change directions quickly while maintaining balance. A 1-inch high obstacle in the shape of a Maltese cross is placed on the floor. The participant is instructed to begin in the back, left quadrant then to move 1) forward, 2) sideways right, 3) backward, then 4) sideways left, then to move in the reverse direction back to the original square. They move as fast as possible through their movement progression while keeping one foot on the floor at all times. The only materials required are pieces of PVC pipe and a stop watch. Participants will complete one practice and two successful trials. In healthy, active duty Service members, inter-rater reliability was excellent (ICC = 0.99, 95% CI = 0.99-0.99) and test-retest reliability was good (ICC = 0.86, 95% CI = 0.75-0.96) [41]. In individuals with amputations, the Four-Square-Step-Test has high sensitivity (92%), specificity (93%) and predictive values (positive: 86%; negative: 96%) for identifying fall risk.

• **Narrowing Beam Walking Test** (NBWT). The NBWT is a reliable and valid task that challenges balance abilities in healthy and impaired populations [42, 43]. Participants walk with arms crossed along a 6.71m beam of narrowing width until they can no longer maintain balance and step off the beam. The distance of the last foot position on the beam is recorded. Five trials can accurately estimate usual balance performance in groups such as lower limb prosthesis users [43]. The NBWT demonstrates strong correlations (0.70-0.85) with performance on other balance tasks such as TUG, FSST, and Berg Balance Scale and moderate correlations (0.49) with the ABC Scale. Performance is significantly lower among individuals of lower mobility levels. There are no floor or ceiling effects indicating that the NBWT measures broad ranging balance abilities without reaching scale limits [42].

• **20-Meter Shuttle Run**. The 20-Meter Shuttle Run has been used in other ESR AFO research [44]. It is a non-standardized measure intended to assess power, deceleration, and ability to change pace [43]. It is used in this study for its resistance to ceiling effects, particularly for high-activity ESR AFO users. Participants will be instructed to move to a cone 10 meters away and then return to the starting point as fast as possible. Each subject will be asked to complete three trials at each point of testing, with up to five minutes of rest between trials. The fastest of the recorded times will be used to score each instance of testing. Participants that are not able to run will be asked to walk as quickly as is safely possible to complete the course and may skip the assessment if otherwise not able to complete.

**Photos and Video** We may take video and photos of participants during portions of this study for documentation and use in research publications. To protect the identity and privacy of our participants, all videos and photos will be edited later to de-identify the images (e.g., blurring of faces, tattoos, and other distinguishing marks). No sound will be recorded to prevent voice identification.

**Additional Use of Coded Data** Throughout the study we may place copies of all coded data in publicly accessible online repositories. Once posted, the coded data will be publicly accessible to search, retrieve, and analyze for any purpose. Participants will be made aware of this use of coded data during the consent process and it will be descried in the consent form. If participants do not wish to have their coded data placed in online repositories they may choose to not participate in the study. We will also share coded data between the research team members at WRNMMC, VAPSHCS, SIBCR, and HJF.

***Potential Risks to Participants*** There is a risk of injury or physical discomfort associated with the device casting, fitting, wear, or testing during study participation. Wearing the emulated AFO may also cause discomfort. There is always the risk that the emulator could fail or stop working properly. This could cause minor soft tissue injury (i.e. soreness, bruising) or other minor injury (i.e. knee or ankle joint soreness). There are built-in emergency stops designed to prevent injury and Humotech currently has 15 emulator systems in use with no reported safety concerns. The risks of the emulator are similar to those of wearing the actual AFO. These risks are considered minimal risks since the activities are consistent with those performed during physical therapy evaluations or AFO fittings, and the devices can be removed at the participant’s discretion. Device fittings will be overseen by a certified prosthetist-orthotist and data collection will be conducted by trained research staff. Furthermore, if a participant cannot safely perform a test once begun, the test will be stopped and the participant will proceed to the next test or try again. If the participants experience any pain or discomfort during or after testing, they will be instructed let the research staff know. Participants may experience fatigue during the assessment sessions. If fatigued, participants will be instructed inform research staff and will be allowed to rest until they are comfortable or decide to discontinue.

There is always the possibility that participants may fall while walking in an AFO but procedures have been put in place to minimize this risk. All study interventions are non-invasive. There may, however, be unforeseen risks associated with this study.

Some of the questionnaires may make participants feel uncomfortable or embarrassed. This is not expected based on the nature of the study, but if they experience these emotions they can decline to answer the questions.

Although we make every effort to keep participants information secret, there is always a chance of loss of confidentiality through someone gaining access to the information that researchers have collected. Section 16 outlines how we will protect your privacy to the best of our ability.

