## 4.6 Data Analysis

**Aim 1.** The purpose of Aim 1 is to test the ability of the AFO emulator to reproduce the user experience of wearing actual AFOs during different activities (walking, running, stair climbing; level ground, ramps) in individuals with lower limb musculoskeletal injury. We will consider the outcome measures as continuous response variables in the statistical analysis. We will evaluate the data from the in-lab actual and in-lab *emulated* sessions using a linear mixed effect (LME) regression with the *emulated* AFO data as the independent fixed effect, the *actual* AFO data as the dependent fixed effect, and subject participant as a random intercept.

**Hypothesis 1A**. In Specific Aim 1A, we are testing the hypothesis that the experimental AFO preference measured during the in-lab *emulated* session will be significantly correlated with the experimental AFO preference measured during the in-lab *actual* session. This model estimates a change in *actual* AFO preference per unit change of *emulated* AFO preference.

**Hypothesis 1B**. In Specific Aim 1B, we are testing the hypothesis that self-reported measures and biomechanics will be significantly correlated between the in-lab *emulated* session and the in-lab *actual* session. This model operates the same as in 1A, substituting measures of function and mobility for preference.

**Aim 2.** The goal of Aim 2 is to determine if the in-lab (*emulated* and *actual*) measurements are a good predictor of the longer-term measurements made following a take home trial. To perform this analysis, we compute a similar LME regression as Aim 1 with the *emulated* *or actual* in-lab AFO data as the independent fixed effect, the *actual* take-home trial AFO data as the dependent fixed effect and subject participant as a random intercept.

**Hypothesis 2A**. In Specific Aim 2A, we are testing the hypothesis that the experimental AFO preference measured during the in-lab *emulated* session will be significantly correlated with the experimental AFO preference measured during the take home-trials. This model operates the same as in 1A, substituting measures of take-home trial preference as the dependent variable.

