# Privacy and Confidentiality

As with any study, it is possible, although unlikely given the impersonal nature of the data collected, that participants may experience a loss or invasion of privacy or confidentiality because of participation in this study. The risk of harm is minimal and the protections described here will be followed.

Participant data will be collected the study sites and will be entered into independent and secure databases. In general, electronic data will be coded with links stored separately, stored on password protected drives, servers will be backed up regularly, firewalls in place, and access permitted only by study team members listed on the approved IRB protocol. Hard copies of data forms will contain only codes and be stored in locked cabinets (dedicated to this study’s records), and locked offices with access only given to study team members. Informed consent documents will be stored separately along with other identifiable information (such as records necessary to have in paper form, which will be limited). Because this is a multi-site study, extra care will be taken not to share PHI or other identifiable information about participants across centers.

To protect privacy and confidentiality during data collections, all data collected will have PHI removed and participants will be issued an alpha-numeric code which will be used to track their records. Subject records will be coded with a unique identifier. The first five characters will be an abbreviation of the study (AFO Test Drive - AFOTD) to identify to which study the subject belongs followed by a site identifier (WR = Walter Reed, VA = VAPSHCS) and sequential numbering based on the subject order of enrollment. The device tested will be indicated as device 1, 2, or 3.

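### The Aim 1 and Aim 2 models omit test position, session order and site, and three AFO sequences cannot balance carry-over; the slope may be biased, in a direction the protocol leaves open

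*Protocol*

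**What the plan says.** Protocol section 4.5 (Study Evaluations) randomises two things in blocks, AFO sequence and session order, so that similar numbers are "assigned to each of three AFO testing sequences and similar numbers of participants undergo either the emulated in-lab session or actual AFO" session first. The three emulated AFOs are described as tried in random order. For the community phase the text reads "Participants will complete two-week long community trials in each of the three actual AFO conditions in a randomized", and the sentence ends there. Section 4.5 does not say which three sequences are used, or whether a participant keeps one sequence through the emulated, actual and community phases. It sets a rest of at least 10 minutes between in-lab conditions and states no washout between community periods.

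Section 4.6 (Data Analysis) specifies the Aim 1 model: the emulated "AFO data as the independent fixed effect, the" actual data as the dependent variable, "and subject participant as a random intercept". For Aim 2, "we compute a similar LME regression as Aim 1", with the take-home data as the outcome. Hypotheses 2A to 2D swap the variables and keep this structure. The null hypothesis in the power paragraph is a slope of zero.

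The section on privacy notes "Because this is a multi-site study, extra care will be taken" with identifiable data, and the participant code carries one of two site identifiers. Site appears in no model.

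**The concern.** The design controls device order and session order, but the analysis uses neither. This matters more here than in a comparison of devices, because the test is of a non-zero slope. Anything that moves the predictor and the outcome together, within or between participants, counts towards agreement. Anything that moves them in opposite directions counts against it.

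Three routes need to be kept apart. A position effect (practice, fatigue) falls on the same device in both sessions only if the orders match or are correlated. Carry-over from the preceding brace can become attached to particular devices if the sequences always place the same brace before each one. Session order and site act between participants. The Aim 1 and Aim 2 conclusions on whether the emulator reproduces or predicts experience with the actual AFO rest on these slopes.

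**Working it through.** **1. The plan's own figures.** 50 × 1.12 = 56.0 reproduces the total of 56 (50 / 0.88 = 56.8 would round up to 57). The power of 97% and 98% cannot be reproduced, because the pilot slope, residual error and alpha are not given. At an assumed two-sided 5% level they imply slope/SE of about 3.84 and 4.01. Nothing below changes the sample size.

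**2. What three sequences can balance.** Three devices have 6 orders, so there are 20 ways to choose three. Three sequences contain 3 × 2 = 6 adjacent pairs, and carry-over balance needs all six ordered device pairs once each. None of the 20 sets achieves this. Only two sets balance position: ABC, BCA, CAB (pairs AB, BC, CA, each twice) and ACB, BAC, CBA (pairs AC, BA, CB, each twice). In both, a device that is not first always follows the same other device.

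**3. Expected within-participant slope with no true association.** Let the residual SD be σ = 1 in each session.

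- Position drift d per position, same order in both sessions: the cross-product per participant is 2d² and the predictor sum of squares is 2σ² + 2d², so the slope is d²/(σ² + d²). For d = 0.25 this is 0.0625/1.0625 = 0.06; for d = 0.5 it is 0.25/1.25 = 0.20. With independent orders the expected cross-product is zero.
- Carry-over of −c, 0 or +c from the preceding device, cyclic sequences, independent orders: each device is non-first in 2/3 of sequences, so its mean shift is 2/3 of its fixed predecessor's effect. The cross-product is 2 × (2c/3)² = 8c²/9. The mean carry-over sum of squares is (2/3 + 2/3 + 2)c²/3 = 10c²/9. At c = 0.5 the slope is 0.222/(2 + 0.278) = 0.10. The leak runs through device means, so a position term does not remove it.
- All six orders, drawn independently: each other device precedes with probability 1/3, so the mean shift is −1/3 of the device's own effect. The cross-product is 2 × (c/3)² = 2c²/9, a quarter of the cyclic value.

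**4. Between-participant routes.** A shift s in whichever session comes second reaches the predictor in one half of participants and the outcome in the other half, so the covariance is −s²/4. A site difference s shared by both sessions, with sites of equal size, gives +s²/4.

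**5. Simulation of the stated model.** REML random intercept, 50 participants, 3 devices, 4,000 datasets per scenario, no true association, |t| > 1.96. Participant SD and residual SD are both assumed to be 1, and all effects are assumptions in residual-SD units. With no effect at all, positive slopes occur in 3.2%.

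| Assumed effect | Sequences | False positive slopes | With added term |
|---|---|---|---|
| Drift 0.1 / 0.25 / 0.5 / 1.0 | cyclic, same order | 3% / 8% / 40% / 100% | position: 2–3% |
| Drift 0.1 to 1.0 | cyclic, independent | about 3% | not needed |
| Carry-over 0.5 / 1.0 | cyclic, same order | 19% / 93% | position: 20% / 92% |
| Carry-over 0.5 / 1.0 | cyclic, independent | 13% / 69% | not run |
| Carry-over 0.5 / 1.0 | six, same order | 20% / 92% | position and carry-over: 3% |
| Carry-over 0.5 / 1.0 | six, independent | 4% / 9% | not run |
| Site 0.5 / 1 / 2 | cyclic, same order | 4% / 11% / 48% | site: 2–3% |
| Second session 0.5 / 1 / 2 | cyclic, same order | 1.7% / 0.5% / 0% | session order: 2–3% |

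A separate simulation gave about 14% and about 5% for 0.5 SD carry-over with independent cyclic and independent six-order designs. In the last row, false negative slopes rise to 4.5% / 10% / 50%. Adding position, session order and site barely affects power: 78.5% becomes 77.6% at a true slope of 0.30.

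**The case against.** The strongest reply is that position, sequence and site covariates are commonly set in a statistical analysis plan, which is not shown, so their absence from a protocol is no fault. That would hold if section 4.6 were silent. It instead names the fixed effect and the random effect and reuses that structure for Aim 2. The number of sequences is a design matter that no analysis plan can repair.

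Second, the protocol calls the emulated order and the community order randomised, which fits separate draws. With separate draws, position drift does no harm. This stands, and it makes the position bias conditional.

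Third, accommodation in the emulator, acclimation in each actual AFO and rest between conditions should reduce drift and carry-over. This also stands. Small drifts are harmless even with a shared order (3% at 0.1 SD), and no document gives a drift or a within-person SD.

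Fourth, the cyclic square is an assumption, because the protocol does not list its three sequences. That is correct; only the impossibility of carry-over balance holds for every choice.

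**Conclusion.** The stated model omits both randomised factors and site, and no set of three sequences can balance first-order carry-over; these two points are certain. That the slopes are inflated is conditional. Position drift inflates them only under a shared or correlated order (about 8% and 40% at assumed drifts of 0.25 and 0.5 SD). Carry-over can do so without a shared order if the sequences are cyclic (13% to 14% at an assumed 0.5 SD). The actual size cannot be derived from the protocol.

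Several stronger readings are tempting and not supported:

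- A reader might infer that the analysis is biased towards success. The protocol neither states nor rules out the shared order this needs for position drift.
- A reader might count emulated-first or actual-first among the effects that imitate agreement. Its sign is negative, so it masks agreement.
- Site is neither randomised nor an order effect. Site and session order are constant within a participant, so the random intercept largely absorbs their outcome variance; the issue is between-participant covariance rather than added noise.
- The carry-over-adjusted variance of a device contrast is 4.0 times larger with cyclic sequences than with all six (1.667 against 0.417 σ² per six participants). Aims 1 and 2 test slopes, so this ratio does not describe their precision.
- About half the participants rate the emulator after the actual AFOs. This is a legitimate counterbalance for Aim 1 and does not invalidate hypothesis 2A.

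The change is worth making because it is specific and nearly free.

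**What to change.** State in section 4.5 which three sequences have been used and whether each participant kept one sequence through all phases. In section 4.6, add test position, session order (emulated first or actual first) and site as fixed effects in the Aim 1 and Aim 2 models.

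For participants still to be randomised, use all six AFO orders, drawn independently for the emulated, actual and take-home phases. Both parts are needed: six orders kept the same across sessions still gave 20% at 0.5 SD carry-over without adjustment. Independent draws of six orders leave a small residue (4% to 5%), so fit a first-order carry-over term as a sensitivity analysis. An estimate for hypothesis 2A in the emulated-first half is an optional supportive analysis.

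The cost is four model degrees of freedom (two for position, one each for session order and site) and a revised randomisation list. There are no extra visits, and the total of 56 is unaffected.
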